## Abstract

**Background:**

Cognitive impairment is present in bipolar disorder (BD) during the acute and remitted phases and hampers functional recovery. However, there is currently no clinically available treatment with direct and lasting effects on cognitive impairment in BD. We will examine the effect of a novel form of cognitive remediation, action-based cognitive remediation (ABCR), on cognitive impairment in patients with BD, and explore the neural substrates of potential treatment efficacy on cognition.

**Methods/design:**

The trial has a randomized, controlled, parallel-group design. In total, 58 patients with BD in full or partial remission aged 18–55 years with objective cognitive impairment will be recruited. Participants are randomized to 10 weeks of ABCR or a control group. Assessments encompassing neuropsychological testing and mood ratings, and questionnaires on subjective cognitive complaints, psychosocial functioning, and quality of life are carried out at baseline, after 2 weeks of treatment, after the end of treatment, and at a six-month-follow-up after treatment completion. Functional magnetic resonance imaging scans are performed at baseline and 2 weeks into treatment. The primary outcome is a cognitive composite score spanning verbal memory, attention, and executive function. Two complete data sets for 52 patients will provide a power of 80% to detect a clinically relevant between-group difference on the primary outcome. Behavioral data will be analyzed using mixed models in SPSS while MRI data will be analyzed with the FMRIB Expert Analysis Tool (FEAT). Early treatment-related changes in neural activity from baseline to week 2 will be investigated for the dorsal prefrontal cortex and hippocampus as the regions of interest and with an exploratory whole-brain analysis.

**Discussion:**

The results will provide insight into whether ABCR has beneficial effects on cognition and functioning in remitted patients with BD. The results will also provide insight into early changes in neural activity associated with improvement of cognition, which can aid future treatment development.

**Trial registration:**

Clinicaltrials.gov, NCT03295305. Registered on 26 September 2017.

**Electronic supplementary material:**

The online version of this article (10.1186/s13063-018-2860-8) contains supplementary material, which is available to authorized users.

## Background

Persistent moderate to severe cognitive impairment across several cognitive domains is seen in 30–70% of patients with bipolar disorder (BD) during periods of remission [1–3]. The cognitive impairment is directly associated with reduced functional capacity and poor occupational outcome [4, 5], with the latter being the greatest economic burden of BD [6]. Despite growing evidence for negative individual and societal consequences of cognitive impairment associated with BD, there is currently no available treatments with direct and lasting effects on cognition [7].

The search for effective treatments for cognitive impairment in BD is adversely related to the lack of a brain-based biomarker for cognitive improvement [8, 9]. In particular, the development of new treatments targeting the central nervous system typically rely on pre-clinical studies, which provide poor prediction of treatment effects in clinical trials [10]. Consequently, clinical trials investigating the pro-cognitive effects of candidate cognition treatments have produced overall disappointing or only preliminary results [7, 11]. However, evidence from a few small open-label, non-controlled studies suggests that cognitive remediation (CR) may have pro-cognitive effects in patients with BD [12, 13], and recent findings from a larger randomized clinical trial of 70 h of computerized CR in remitted patients with BD type I showed improvements on processing speed, visual learning, and memory and a cognitive composite measure [14].

We have previously conducted the first randomized, controlled clinical trial investigating the effect of a 12-week CR program in partially remitted patients with BD [15]. The treatment showed no effect on objective cognitive measures (primary outcome), although some aspects of subjective cognition improved [15]. This lack of efficacy could reflect a type 2 error, as it was not verified whether the patients had objectively measured cognitive impairment at enrolment and post hoc assessments revealed no objective impairment (in the group as a whole) in the targeted cognition domain (verbal memory), sustained attention, or executive function [15]. As accumulating evidence indicates that there is only a weak association between subjective cognitive complaints and objective cognitive impairment in patients with BD [16, 17], potential cognitive benefits could have been masked by ceiling effects. However, it is also conceivable that the CR treatment was not intense enough and relied too heavily on *compensatory strategies* rather than *intensive training* of cognitive skills. A new form of CR, action-based cognitive remediation (ABCR), aims to optimize traditional CR to promote cognitive flexibility and to transfer skills acquired during treatment sessions to patients’ everyday lives. It involves individual goal setting, an intense training program combining computerized training with practical in-session activities, and cognitively challenging tasks between sessions, and has shown promising effects [18]. Specifically, Bowie et al. [18] compared ABCR (*N* = 24) to traditional CR (*N* = 26) in a patient group with severe mental illness, including patients with BD. While both treatments improved cognition, ABCR had a greater effect on functional capacity than traditional CR [18]. This converges with a meta-analysis on CR trials in schizophrenia showing that the combination of CR and skills training had larger effects on patients’ functional capacity than CR alone [19]. The adaptation of ABCR to patients with BD may, therefore, not only improve cognitive skills but also increase patients’ functional capacity, with benefits for quality of life and societal costs.

Patients with BD in remission display aberrant (most consistently hypo-) activity in areas including the dorsolateral prefrontal cortex (dlPFC) and the ventrolateral prefrontal cortex during cognitive control tasks like working memory and strategic encoding [20, 21]. Changes in neural activity in the dlPFC have been observed in interventions demonstrating possible pro-cognitive effects in psychiatric disorders. In particular, a recent meta-analysis assessing the changes in neural activity following CR treatment in schizophrenia found increased activity in the lateral and medial prefrontal cortex to be the most robust indicator of treatment-associated cognitive improvement [22]. Our group has demonstrated changes in neural activity in dorsal and dorsomedial prefrontal areas during working memory and learning tasks following 8 weeks of weekly high-dose erythropoietin (EPO) vs. saline infusions in patients with affective disorders [23, 24]. These findings indicate that changes in the neural activity in the dorsal prefrontal cortex may be a possible biomarker for pro-cognitive effects of interventions targeting cognition.

### Aims and hypotheses

This study aims to assess the effect of ABCR vs. a control treatment on cognitive improvement in (i) BD patients in full or partial remission and to (ii) assess early neural changes indicative of potential treatment benefits on cognition.

We hypothesize (i) that ABCR vs. a control treatment has a beneficial effect on cognition in patients with BD in full or partial remission (the primary hypothesis of the study). We hypothesize (ii) that this treatment-associated improvement of cognition translates into better functional capacity at the 6-months follow-up assessment (secondary outcome). For the *exploratory* analysis of the neuronal underpinnings of these treatment effects, we hypothesize that ABCR will produce an early change in neural activity in the dorsal prefrontal cortex during working memory and strategic memory encoding in the direction of the prefrontal activity levels seen in a healthy control group (i.e., partial normalization) and this activity will correlate with ABCR-associated improvements in cognitive function.

## Methods/design

### Study design and participants

See Fig. 1 for a flow diagram of the trial. The project has a randomized, controlled, outcome-assessor-blind, parallel-group design. The trial will include outpatients with BD in full or partial remission (score ≤ 14 on the Hamilton Depression Rating Scale [25] and Young Mania Rating Scale [26], respectively). No criteria for the duration of symptom stability is applied due to the feasibility of this group-based intervention trial, which requires starting groups three times per year. However, current mood symptoms and patients’ retrospective period of symptom stability will be recorded. Recruitment will be carried out through the ongoing Bipolar Illness Onset study [27], the Copenhagen Affective Disorder Clinic (Psychiatric Centre Copenhagen, Rigshospitalet), other mental health centers, consultant psychiatrists in the Capital Region of Denmark, and through advertisements on relevant websites.

**Fig. 1 Fig1:**
[figure not shown]
Flow diagram

Eligible participants must be between 18 and 55 years, be fluent in Danish, and present with *objective* cognitive impairment corresponding with a total score below the cutoff or scores below the cutoff on a minimum of two out of the five subtests (verbal learning test – immediate, working memory test, verbal fluency test, verbal learning test – delayed, and processing speed test) on the Screen for Cognitive Impairment in Psychiatry—Danish version (SCIP-D) [17, 28]. Patients are eligible if they have an ICD-10 diagnosis of BD (types I and II) confirmed using the Schedules for Clinical Assessment in Neuropsychiatry interview [29]. Their daily use of benzodiazepines will be tapered to a maximum dose equivalent to ≤22.5 mg oxazepam or ≤7.5 mg diazepam per day (cutoffs for doses with limited cognitive side effects). Other than that, patients are requested to avoid significant changes to dose and type of any medication prior to or during the study if possible. Any changes will be recorded at treatment completion and at the 6-month follow-up.

Exclusion criteria are current drug or substance abuse (up to 3 months prior to inclusion), previous serious head trauma, neurological illness, schizophrenia or schizoaffective disorder, dyslexia, claustrophobia, having a pacemaker or other metal implants inside the body, and electroconvulsive therapy in the 3 months prior to inclusion. Female participants are not included if they are pregnant. All participants must provide written informed consent, which includes consent to collection of biological material and for data to be used in ancillary studies. See Additional file 1 for a trial protocol checklist.

### Procedure

Upon their first visit to the Copenhagen Affective Disorder Research Center (CADIC), participants are informed about the project and provide written informed consent after which they undergo an eligibility assessment. The written informed consent will be obtained by the first author. Upon inclusion, participants are randomized with stratification for gender and age (< or ≥ 35 years) to either 10 weeks of ABCR (active treatment) or patient group (control treatment). When 4–6 participants have been randomized to a group, baseline assessments will be carried out in the week prior to the first group session. Deterioration in terms of clinical symptoms at the baseline assessment is recorded, but participants are not excluded if their symptoms worsen. The baseline assessment is completed over two days, 1–3 days apart for practical reasons and to avoid attrition.

On day 1, participants’ mood is rated with the Hamilton Depression Rating Scale and Young Mania Rating Scale, followed by a functional magnetic resonance imaging (fMRI) scan encompassing spatial and verbal working memory N-back tasks, a picture encoding task, a resting state, and a structural scan. On day 2, participants attend the research center in the morning for a fasting blood test. A comprehensive neuropsychological test battery is administered by a treatment-blinded outcome assessor. Participants fill in questionnaires concerning subjective cognitive complaints, psychosocial functioning, and quality of life. Functional capacity is assessed using a clinician-rated interview and a performance-based assessment. Finally, sleep quantity and quality in the past 3 days is assessed.

After 2 weeks of ABCR or control treatment, the fMRI, neuropsychological testing, and an assessment of mood and subjective cognition are repeated to assess whether early task-relevant neural activity changes—prior to improvement on the behavioral measures of cognition—correlate with and predict subsequent cognitive improvement after treatment completion. The neuropsychological assessments and questionnaires, as well as assessments of functional capacity and quality of life, are repeated within 2 weeks after treatment completion (primary outcome assessment time), and 6 months after treatment completion. An intermediate clinical mood rating is performed during week 6.

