## Discussion

The present study investigates the effect of ABCR on cognitive improvement in clinically stable BD patients. It also explores early treatment effects on dorsal prefrontal activity to examine neurocircuitry target engagement. This will contribute to the broader aim of identifying a neurocircuitry biomarker model for pro-cognitive effects.

All participants are required to present with objective cognitive impairment to be enrolled in the study. The criteria are based on findings from our previous EPO trials, showing that patients with worse objective cognitive functioning at baseline have the greatest chance of achieving treatment efficacy [50] and on the subsequent methodological recommendations for cognition trials in BD by the Targeting Cognition Task Force of the ISBD [44]. The criteria will serve to ensure that the sample is enriched for cognitive impairment, which will enhance the chances of detecting treatment-associated cognitive improvement [9]. However, it could cause a recruitment challenge since it is estimated that 30–70% of euthymic patients with BD show clinically relevant objective cognitive impairment [1–3]. As the study will recruit up to 58 patients with BD in full or partial remission to ensure complete data sets for 52 patients, multiple recruitment channels have been identified: psychiatric centers run by Mental Health Services in the Capital Region of Copenhagen, consultant psychiatrists, advertisements, and the Copenhagen Affective Disorder Clinic in Rigshospitalet. A break will interleave the fifth and sixth session in the ABCR program with sessions occurring twice a week, to ensure that all ABCR participants are assessed with fMRI and neuropsychological tests following 2 weeks (four sessions) of treatment.

There are no known direct risks associated with participation in the study. All participants are covered by public insurance provided by the Patient Compensation Association. The use of a control group, where participants are not offered treatment targeting cognitive impairment, will control for non-specific therapeutic effects of being in a group setting, which may increase participants’ quality of life and functional capacity. The use of a control group is also rendered necessary, as there is currently no effective treatment for cognitive impairment with direct and lasting effects [9].

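### The conclusions are worded for clinically stable, remitted patients, but the design secures only mood scores of 14 or less at eligibility

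*Protocol article*

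**What the plan says.** **Population named.** Under Aims and hypotheses, the primary hypothesis is that "ABCR vs. a control treatment has a beneficial effect on cognition in patients with BD in full or partial remission". The Discussion paragraph of the Abstract says the results will show "whether ABCR has beneficial effects on cognition and functioning in remitted patients with BD". The main Discussion goes further: "The present study investigates the effect of ABCR on cognitive improvement in clinically stable BD patients".

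**Population enrolled.** Study design and participants admits "outpatients with BD in full or partial remission (score ≤ 14 on the Hamilton Depression Rating Scale" and the same limit on the Young Mania Rating Scale. It then states: "No criteria for the duration of symptom stability is applied due to the feasibility of this group-based intervention trial", the reason being that the format "requires starting groups three times per year". Current mood and the past period of stability are to be recorded.

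**Sequence.** According to Procedure, patients are randomized on inclusion. Baseline follows when 4–6 have been randomized to a group, in the week before the first session. On worsening in that interval the section says: "Deterioration in terms of clinical symptoms at the baseline assessment is recorded, but participants are not excluded if their symptoms worsen". Mood is rated on baseline day 1, after 2 weeks of treatment and in week 6.

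**Use of mood in analysis.** The article names adjustment for mood only in the conditional regression for the imaging data (Strategic picture encoding). Statistical analyses says mixed models will be used for the behavioral outcomes and lists no covariates.

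**The concern.** The population that the Discussion names and the population that the procedures produce are not the same. A patient can meet the mood criterion once, wait for a group to fill, be in a mood episode when the baseline composite is measured, and still be in the trial. Nothing in the design makes the sample stable, or guarantees that it is still in remission when treatment starts.

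This can touch the primary outcome as well as the wording. The Abstract says cognitive impairment is present in acute as well as remitted phases. If cognition is additionally lowered during an episode, which the article does not quantify, some patients will gain on the composite as the episode resolves, whatever their treatment. That would add spread to the change scores and inflate the change seen within each arm. At stake are whether the conclusion describes the patients actually studied, and a modest part of a power margin that is already thin.

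**Working it through.** **1. How old the eligibility rating can be.** With three group starts a year, starts are about 52 / 3 ≈ 17 weeks apart. A patient who just misses a start could wait about that long between the mood criterion and baseline. This interval is inferred; the article does not state it.

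**2. The plan's own power figure.** Inputs from Sample size and power calculation: difference 0.4, 26 per arm, two-sided alpha 0.05, t-test, 10% drop-out. The stated 0.5 is called a mean change, but the power figure reproduces only if it is read as the SD of change.
- Standard error of the difference = 0.5 × √(2/26) = 0.139.
- Noncentrality = 0.4 / 0.139 = 2.88 on 50 degrees of freedom, giving power 0.807 (normal approximation 0.822). With 25 per arm it is 0.791, so 26 is the smallest number above 80%.
- 52 / 0.9 = 57.8, rounded up to 58.

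The stated figures reproduce, with almost no slack.

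**3. Effect of recovery from worsening.** The article gives neither the share who worsen nor the gain on recovery, so both are assumed. Let a share p of each arm regain an extra g on the composite, equally in both arms. Then

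SD of change = √(0.25 + p(1 − p)g²)

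SD of the chance imbalance in the arm difference = g × √(2p(1 − p)/26)

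| p | g | SD of change | Power, 26 per arm | Shift in each arm (p × g) | SD of chance imbalance |
|---|---|---|---|---|---|
| none | none | 0.500 | 0.807 | 0 | 0 |
| 10% | 0.25 | 0.506 | 0.799 | 0.025 | 0.021 |
| 10% | 0.50 | 0.522 | 0.773 | 0.050 | 0.042 |
| 20% | 0.25 | 0.510 | 0.792 | 0.050 | 0.028 |
| 20% | 0.50 | 0.539 | 0.747 | 0.100 | 0.055 |

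At a more extreme p = 30% and g = 0.75, the SD is 0.607 and power 0.645.

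**4. Is the contrast biased?** The shift p × g is the same in both arms and cancels in the difference. In 40,000 simulated trials with no treatment effect, the mean arm difference was −0.001 (p = 20%, g = 0.5) and 0.001 (p = 30%, g = 0.75). The rejection rates were 0.051 and 0.049. Each arm nevertheless rose by 0.10 and 0.23 respectively. Recovery therefore inflates within-arm change and adds noise, and it leaves the type I error of the comparison intact.

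**The case against.** The strongest reply is that the choice is open and reasoned. The article says no stability period is required, gives the group format as the reason, records mood repeatedly, and keeps worsened patients because they are already randomized; removing them would breach intention-to-treat. The aims, the Abstract's methods paragraph and the eligibility text all speak of full or partial remission, and clinically stable appears only once. A condensed article also need not list its covariates. All of this stands. Keeping these patients is not the error, and the absent mood covariate is not a defect, since the full protocol or an analysis plan may supply it. But a feasibility reason for having no stability criterion does not justify calling the sample stable afterwards.

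A reader might infer something stronger: that recovery from episodes biases the primary result, through imbalance between two small arms. Suppose 8 patients have worsened. Their counts in the two arms of 26 then differ by 4 or more in 25% of allocations, and a 6:2 split with a rebound of 0.5 moves the difference by (6 − 2)/26 × 0.5 = 0.077, about 19% of the 0.4 target. The arithmetic is correct, but the inputs are assumed and the shift is 0.077/0.139 = 0.55 of one standard error. Under 1:1 randomization it is random error that the standard error already carries. Bias would need worsening or recovery to differ systematically by arm. That is conceivable, because baseline follows allocation and patients know their group, but the article gives no evidence of it.

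**Conclusion.** The concern holds as a mismatch between the population named in the conclusions and the one the design secures. Clinically stable contradicts the absence of any stability criterion and the retention of worsened patients. Remitted is accurate only as of the eligibility assessment. This part rests on the text alone and needs no assumption.

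The statistical cost is lost precision. Over assumed ranges of 10–20% worsening and a regain of 0.25–0.5, power goes from just above the claimed 80% to just below it at the mild end and to about 75% at the other. If few patients worsen, or cognition does not rebound, the loss is negligible. The randomized comparison remains valid under any of these values as long as worsening and recovery do not depend on arm.

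**What to change.** Leave enrolment and the intention-to-treat set unchanged.

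1. In the Abstract's Discussion paragraph and in the main Discussion, describe patients as in full or partial remission at the eligibility assessment, and drop clinically stable. This costs only wording.
2. Report by arm how many patients score above 14 on either mood scale at baseline. The data are already collected, and the table would also show any difference that arose after allocation.
3. Include baseline Hamilton and Young scores as covariates in the mixed models for the composite and for the Functional Assessment Short Test, to recover precision. This costs two degrees of freedom. The gain depends on how strongly mood relates to change, which is unknown here. The ratings are taken after allocation, although before the first group session, and the text should say so.
4. If an analysis limited to patients still at 14 or less on both scales at baseline is wanted, label it a sensitivity analysis only. It is smaller, and it selects on a variable measured after randomization, so it does not carry the full protection of the randomized comparison.
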